### Study objectives and outcome measures

The primary study objectives and outcome measures are:Assessment of treatment efficacy of imiquimod treatment for high-grade CIN, as compared to LLETZ treatment. Successful treatment for the experimental (imiquimod) arm is defined as regression to CIN 1 or less in diagnostic biopsies at 20 weeks follow-up. Successful treatment for the LLETZ arm is defined as normal cytology at 6 months follow-up. Based upon earlier studies, we hypothesize that 50–75 % of patients in the experimental (imiquimod) arm will show regression to CIN 1 or less.These two different outcome measures (cytology in the LLETZ arm and histology in the experimental arm) were selected in order to optimize the assessment of treatment efficacy, whilst limiting overtreatment of patients (performing unnecessary biopsies or LLETZ treatments). For the experimental arm, it is assessed by colposcopy with diagnostic biopsies and for the LLETZ arm it is assessed by cytology. Regarding efficacy of LLETZ treatment, the significance of resection margins of the LLETZ specimen is controversial and is not advised in guidelines as outcome measure of LLETZ efficacy. Therefore, regular follow-up cytology at six months was selected as outcome measure, as is also done in clinical practice. Regarding imiquimod treatment, histological assessment of treatment efficacy was selected as outcome measure, in order to optimize the assessment of potential residual disease. Biopsies were chosen rather than a standard LLETZ procedure to evaluate residual disease, to prevent overtreatment.Development of a biomarker model to predict adequate response to imiquimod treatment.

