Secondary study objectives and outcome measures are:To determine the incidence and severity of side effects of LLETZ and imiquimod therapy, scored by the Common Terminology Criteria for Adverse Events guidelines.To estimate disease recurrence rates for both arms at 6, 12 and 24 months follow-up, defined as abnormal cervical cytology. The follow-up term starts after treatment is finished.To assess Quality of life (QoL) for both arms before, during and after treatment (at 0 and 20 weeks and after 1 year) by the following QoL questionnaires: [1] Medical Outcomes Study 36-Item Short-Form General Health Survey (RAND 36), to assess generic health-related quality of life, [2] the European Organization for Research and Treatment of Cancer (EORTC) QLQ-C30, to assess cancer-specific health-related quality of life, and [3] the European Organization for Research and Treatment of Cancer (EORTC) QLQ-CX24, to assess cervical cancer specific quality of life, including sexual functioning.

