### Sample size calculation

The sample size calculation was based on a regression rate of 73 % at 20 weeks follow-up after immunotherapy and a 95 % treatment efficacy of LLETZ. Using 80 % power and alpha = 5 %, the estimated sample size required is 42 women in both arms. Allowing for a withdrawal rate of approximately 20 %, 53 women will have to be recruited in each arm. Sample size calculations for the secondary outcome measures indicated that roughly 70 patients per treatment arm would be necessary. Although the sample size calculation should be based on the primary outcome measure, we decided to recruit a total of 140 patients (70 per arm).

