### Statistical methods

Logistic regression analysis will be used to evaluate treatment efficacy of imiquimod treatment, compared to LLETZ treatment. Covariates in this analysis are age at diagnosis, CIN grade, smoking and HPV-subtype. Analysis will be based on intention-to-treat protocol. A biomarker prediction model for adequate response to imiquimod treatment will be developed by backward logistic regression analysis of biomarkers based on likelihood ration tests. The prevalence and severity of side effects of imiquimod and LLETZ treatment will be presented as proportions and means with 95 % confidence intervals. Differences in the rates of overall side-effects and severe side-effects between the imiquimod and LLETZ arms will be tested with a chi-square test. Disease recurrence rates after 6, 12 and 24 months will be evaluated in successfully treated patients by use of multiple logistic regression analysis, after adjustment for age at diagnosis, CIN grade, smoking, sexual behaviour and HPV subtype. Repeated-measures analysis of variance will be used to test for between-group differences over time in Quality of Life scores. Analysis of covariance will be used to compare group scores on these outcomes at 20 weeks and at 12 months, with adjustment for baseline scores.

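### The recurrence model fits arm plus five covariates in about 94 to 118 women with probably few events, so ordinary maximum likelihood risks instability; a penalised fit should be prespecified

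*Protocol article*

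**What the plan says.** Statistical methods in the Protocol article fixes the method and the population: "Disease recurrence rates after 6, 12 and 24 months will be evaluated in successfully treated patients by use of multiple logistic regression analysis". The adjustment set is fixed in the same sentence, where the model is to be fitted "after adjustment for age at diagnosis, CIN grade, smoking, sexual behaviour and HPV subtype". It does not say how any covariate is coded and makes no provision for sparse events. Data collection records HPV genotyping and sexual behaviour at baseline, also without categories.

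Under Study objectives and outcome measures, the secondary objective is "To estimate disease recurrence rates for both arms at 6, 12 and 24 months follow-up, defined as abnormal cervical cytology". The same section sets a different success criterion for each arm. For imiquimod it is "regression to CIN 1 or less in diagnostic biopsies at 20 weeks follow-up". For LLETZ the rule reads: "Successful treatment for the LLETZ arm is defined as normal cytology at 6 months follow-up".

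Sample size calculation assumes a "regression rate of 73 % at 20 weeks follow-up after immunotherapy and a 95 % treatment efficacy of LLETZ", allows for about 20% withdrawal and sets recruitment at 70 per arm. No recurrence rate or expected number of recurrences appears anywhere.

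**The concern.** What a logistic model can support depends on the number of events more than on the number of women. Here the sample is cut to treatment successes, and the outcome may be infrequent among them, yet the model carries arm plus five covariates. When events are few for the number of coefficients, maximum likelihood can separate: a covariate level with no events, or only events, sends its coefficient to infinity. Short of that, estimates are imprecise and tend to lie too far from the null. In practice the analyst then drops covariates after seeing the data.

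The Background calls long-term outcomes after imiquimod unknown, and the Discussion lists long-term recurrence among the study's aims. This model would supply the main between-arm evidence on that question.

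**Working it through.** **The plan's own figure.** The primary sample size for 73% v 95%, two-sided 5%, 80% power, pooled variance is

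n = [1.96·√(2·0.84·0.16) + 0.8416·√(0.73·0.27 + 0.95·0.05)]² / 0.22² = (1.016 + 0.416)² / 0.0484 ≈ 42.4 per arm.

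The plan states 42, and 42/0.8 = 52.5, rounded up to its 53. So the figure is reproduced. There is no plan figure for recurrence events to reproduce.

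**Women in the recurrence model** (70 per arm; success rates and withdrawal from Sample size calculation):
- After 20% withdrawal: 56 × 0.73 + 56 × 0.95 = 40.9 + 53.2 ≈ 94.
- No withdrawal: 70 × 0.73 + 70 × 0.95 = 51.1 + 66.5 ≈ 118.
- At the 50% lower end of the hypothesised imiquimod success: 28 + 53.2 ≈ 81, or 35 + 66.5 ≈ 102.

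**Coefficients.** Arm plus five covariates gives at least 6 excluding the intercept. A three-level sexual-behaviour variable and a five-level HPV variable would make 10. The coding is an assumption.

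**Events per coefficient.** The recurrence rate is also an assumption. At 5%, 94 × 0.05 = 4.7 events; at 20%, 118 × 0.20 = 23.6. With 6 coefficients that is 4.7/6 ≈ 0.8 to 23.6/6 ≈ 3.9. Even 40 events give 40/6 = 6.7.

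**Behaviour of maximum likelihood.** Simulation of 1,500 runs per setting, 41 + 53 women, true odds ratio 2. Log odds ratios of 0.2, 0.5 and 0.4 were assumed for age, CIN grade and smoking, and none for the rest. Percentiles cover runs with a finite arm coefficient.

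| Coefficients | Expected events | Any coefficient separates | Arm coefficient separates | Median odds ratio (10th–90th percentile) |
|---|---|---|---|---|
| 6 | 5 | 45% | 15% | 2.04 (0.48–8.58) |
| 6 | 10 | 6% | 1.5% | 2.04 (0.73–5.73) |
| 6 | 20 | 0.1% | 0% | 2.07 (0.95–4.65) |
| 10 | 5 | 97% | 14% | 2.54 (0.51–17.24) |
| 10 | 10 | 75% | 1.6% | 2.31 (0.74–8.53) |
| 10 | 20 | 27% | 0% | 2.25 (1.02–5.56) |

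A second simulation (94 women, true log odds ratio 0.69, covariate effects again assumed) had the model fail in 48%, 6% and 0% of runs at 5, 10 and 20 events with 6 coefficients, and in 83%, 43% and 8% with 10. The two agree closely at 6 coefficients. At 10 they show how far the answer depends on unstated coding and covariate assumptions. In the second simulation a Firth penalty converged in every run and removed most of the bias. At 20 events with 6 coefficients it cut the root mean squared error of the log odds ratio from 0.63 to 0.55.

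**Share due to the covariates.** In a third set (600 runs, 7 coefficients, odds ratio 2), 5% recurrence after LLETZ implies 9.5% after imiquimod, so 53 × 0.05 + 41 × 0.095 ≈ 6.5 events. The full model failed or separated in 39% of runs, arm alone in 9%. At 10% after LLETZ (about 13 events) the figures were 3% and 0.5%.

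**Six months.** A LLETZ success has normal cytology at 6 months; a 6-month recurrence is abnormal cytology at 6 months. Data collection lists one cytology at that time. If it serves both purposes, the LLETZ arm has zero events by construction, and the arm odds ratio has no finite maximum-likelihood estimate whatever the covariates.

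**The case against.** **The event count is assumed and may be too low.** Recurrence is any abnormal smear, while imiquimod success allows residual CIN 1. The earlier randomised trial cited in the Background had 73% regression but 47% complete remission. So up to 26 points of the imiquimod arm (56 × 0.26 ≈ 15 women, or 70 × 0.26 ≈ 18) could be successes without complete remission. If all had abnormal smears, that arm alone would give 15 to 18 events. This stands, and it is why the count is given as a range. It does not remove the problem, because 40 events still leave fewer than 7 per coefficient.

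**Coding and estimator may be settled elsewhere.** HPV subtype and sexual behaviour could each be binary, and an analysis plan could specify a sparse-data method. That is fair as far as it goes. But the article does fix the regression, the covariate list and the restricted population, and these create the difficulty. Read plainly, multiple logistic regression means ordinary maximum likelihood.

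**At the favourable end the model works.** With 20 events and 6 coefficients separation is almost absent and bias small. A reader might infer that the recurrence odds ratio will be inflated or inestimable; neither the documents nor the simulations support that as a certainty. The breakdown figures also mostly concern covariate coefficients, with the arm coefficient often still finite.

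**Fewer covariates is not plainly better.** A reader might infer that adjustment should give way to an unadjusted difference. That does not follow. The successfully treated are selected after randomisation, by criteria that differ between arms, so randomisation no longer protects the comparison and adjustment has a purpose.

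**Conclusion.** The point holds as a conditional risk. Arm plus five covariates is a heavy model for about 94 to 118 women. At an assumed 5% to 20% recurrence it has roughly 0.8 to 4 events per coefficient with six coefficients, and fewer with more. Separation is common at 5 events, appreciable at 10 events or with about ten coefficients, and near zero at 20 events with six.

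The denominators rest on the protocol's own figures. The recurrence rate, the coding and the simulated covariate effects are assumptions. The 6-month problem is separate and does not depend on the event rate, only on whether one smear defines both success and recurrence. Recurrence is a secondary outcome, so this is a change that should be made but does not threaten the primary analysis.

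**What to change.** In Statistical methods:

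1. Fit the adjusted recurrence model at 12 and 24 months by Firth-penalised logistic regression with profile-likelihood confidence intervals.
2. State the coding of each covariate with as few levels as possible, for example HPV subtype as binary.
3. Report recurrence proportions by arm with 95% confidence intervals beside the model at those two times.
4. Treat any further cut in the covariate list as optional, and prespecify it.
5. Drop the 6-month between-arm recurrence comparison, or redefine it so that the smear establishing LLETZ success is not also the smear that counts recurrence. A 6-month difference in proportions would carry the same artefact.

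The cost is slight shrinkage of the estimate and a little more analysis work. No patients or visits are added.

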### Withdrawal of individual subjects and replacement

Subjects can leave the study at any time for any reason, without consequences. The investigator can decide to withdraw a subject from the study for medical reasons. Withdrawn individuals are not replaced by a new volunteer. Patients who withdraw from the study are offered the standard treatment of CIN, being a LLETZ procedure with standard follow up.

### Ethical considerations and dissemination

The study was approved off by the Medical Ethical Committee of Maastricht University Hospital, University of Maastricht. The study will be performed according to the standards outlined in the Declaration of Helsinki. Ethics committee approval has been completed. Monitoring of the study is performed by a Data and Safety Monitoring Board, appointed by the Clinical Trial Center Maastricht. Adverse events are recorded and reported according to local protocol. Study results will be offered for publication in an international medical journal. Study results will be communicated to trial participants by mail, if agreed upon by the participant.

### Substantial amendment

The current study protocol includes a substantial amendment to the original study protocol, which consisted of three study arms: imiquimod treatment arm, LLETZ treatment arm and an observational arm. The purpose of the observational arm was to assess spontaneous regression of high-grade CIN and to develop a prognostic biomarker panel to predict spontaneous regression of high-grade CIN. Patients in the observational arm underwent no treatment for a period of maximum 20 weeks. Histological assessment of disease development was performed after 10 and 20 weeks by colposcopy with diagnostic biopsies. Inclusion of patients into the study was hampered by the observational arm: patients declined the study because they wished to be treated, rather than undergo observational management. The observational arm was removed from the study.

## Discussion

The development of a non-invasive treatment modality for high-grade CIN lesions may diminish complications as a result of surgical intervention. An earlier study indicates that imiquimod induces disease regression in 73 % [7, 13]. Thus, imiquimod treatment may prevent surgical treatment in the majority of patients. The current study aims to test the treatment efficacy hypothesis as well as long term disease recurrence after treatment and clinical applicability of imiquimod treatment, defined as side effects and quality of life during and after treatment. Furthermore, it aims to develop a prediction model for clinical response to imiquimod treatment, based on histological biomarkers.

### Trial status

First approved by the Medical Ethical Committee Maastricht University 1Hospital, University of Maastricht, on 21 May 2014. Recruitment started in December 2014. Protocol version 5.0.

## Abbreviations

CIN: cervical intraepithelial neoplasia
LLETZ: large loop excision of the transformation zone
HPV: human papillomavirus
VIN: vulvar intraepithelial neoplasia
